**MI and upper limb function**
Correlations between MI and functional tests (Box and Block Test; Jebsen-Taylor Hand Function Test subtests; Functional Reach Test; and Disabilities of the Arm, Shoulder, and Hand questionnaire) will be analyzed using Pearson or Spearman correlation, depending on normality.Regression analyses will examine the predictive effect of MI on function, adjusting for age, dominance, and residual limb length.

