### Outcome Measures

According to the study hypothesis, the primary outcome is MIA assessed using the MIQ-3, which was selected as the primary end point given its central role in prosthetic motor control, motor learning, and functional adaptation in individuals who have undergone transradial amputation.

The secondary outcomes include the following:

Upper-limb functional performance, assessed using the Box and Block Test (BBT), Jebsen-Taylor Hand Function Test (JTHFT), and the Disabilities of the Arm, Shoulder, and Hand (QuickDASH) questionnaireMI performance indicators, including the Mental Chronometry Test (MCT) and hand mental rotation task, as secondary measures of MIAProprioceptive and sensorimotor accuracy, measured by joint position sense (JPS) error using a validated digital goniometer app (DrGoniometer [CDM SrL])General balance and flexibility, evaluated by the Functional Reach Test (FRT) as an indicator of overall functional stabilityCognitive and psychological screening, including the Standardized Mini-Mental State Examination (SMMSE), Beck Depression Inventory (BDI), and Visual Analog Scale (VAS) for pain intensity

Each participant will be assessed once, as this is a cross-sectional study with no intervention. To minimize potential bias, all assessments will be performed by trained evaluators following standardized protocols. Participants will be recruited according to predefined eligibility criteria to reduce selection bias, and data will be systematically recorded to prevent information bias. As no intervention is applied, performance bias is not applicable.

To minimize the risk of type I error resulting from multiple comparisons, the Bonferroni correction will be applied to secondary outcome analyses.

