### SMMSE Description

The SMMSE is a brief 30-item test designed to assess cognitive functions, including attention, memory, orientation, calculation, language, and visuospatial skills. In this study, it will be used solely for participant eligibility screening. Individuals scoring 26 or higher will be included [28].

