### JTHFT Description

The JTHFT, originally developed by Jebsen et al [36], will be used as a performance-based assessment to evaluate hand function in activities of daily living. The test will include various types of grasps and will assess the speed at which participants complete specific tasks. Standardized materials, which will be readily available in clinical settings, will be used for the test. Participants will be required to complete 7 distinct tasks: writing, turning over cards, picking up small objects, simulated feeding, stacking checkers, picking up large light objects, and picking up large heavy objects. Each task will be performed separately with both the dominant and nondominant hands. The test score will be calculated based on the time taken by participants to complete each task (Figure 3).

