**Motor imagery (MI) variables**
Measures will include the Movement Imagery Questionnaire-3, including its subscales: kinesthetic MI, internal MI, external MI, and total score as well as the Orientate app accuracy and completion time, and motor execution time–MI time for the dominant and nondominant hand.Comparisons will be performed using the analysis of covariance, adjusting for age, dominance, and residual limb length.If the analysis of covariance assumptions are not met, nonparametric alternatives will be applied.

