**MI and proprioception**
Correlations between MI and proprioception measures (elbow 30°, 60°, and 90°, and shoulder 90° flexion and abduction) will be conducted.Regression models will evaluate predictors of proprioceptive performance, with covariates age, dominance, and residual limb length.

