**Missing data, outliers, and multiple comparisons**
Missing data will undergo listwise deletion.Trials with outlier values exceeding 2 SDs from the group mean will be excluded. Sensitivity analyses with and without outliers will be performed.The Bonferroni correction will be applied for multiple comparisons.

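### The imagery–function and imagery–proprioception analyses form a grid of up to 120 pairs under plain Bonferroni, with no key pair named and no family fixed, so this objective is poorly powered as planned

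*Protocol article*

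**What the plan says.** The Objective in the Abstract has two parts: comparing imagery ability with healthy controls, and relating it to upper extremity function and proprioception. Textbox 2 sets out the second part in two blocks. The function block plans "Correlations between MI and functional tests (Box and Block Test; Jebsen-Taylor Hand Function Test subtests; Functional Reach Test" and the arm, shoulder and hand questionnaire). The proprioception block says "Correlations between MI and proprioception measures (elbow 30°, 60°, and 90°, and shoulder 90° flexion and abduction) will be conducted". Each block then adds regressions adjusted for age, dominance and residual limb length.

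The imagery measures are listed in the Textbox 2 block on MI variables. For the MIQ-3 they are "kinesthetic MI, internal MI, external MI, and total score"; the others are "Orientate app accuracy and completion time, and motor execution time–MI time for the dominant and nondominant hand".

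Multiplicity is addressed twice. Outcome Measures says "the Bonferroni correction will be applied to secondary outcome analyses". Textbox 2 says "The Bonferroni correction will be applied for multiple comparisons". Neither gives a family or a divisor. The Significance block sets a two-sided .05 threshold for all tests.

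Outcome Measures also lists the SMMSE, BDI and VAS among the secondary outcomes. The SMMSE Description says that "it will be used solely for participant eligibility screening", and the BDI and VAS descriptions give entry cut-offs.

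**The concern.** Bonferroni divides the error rate by the number of tests, so a large grid in a small sample leaves little power for any one link. The plan does not say how many tests are counted. The two multiplicity statements also differ in scope: one is confined to secondary outcomes, the other covers multiple comparisons generally. It is unclear whether a pair that joins the MIQ-3, the primary outcome, to a functional test falls under the first. The same observed correlation could then be reported as a finding or as a null result, depending on a count settled after the data are in. Each link is examined by both a correlation and an adjusted regression, and neither is said to decide. At stake is whether the study can say anything reliable about its association objective.

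**Working it through.** **No figure to reproduce.** The sample-size calculation under Participants concerns the group comparison only. No target correlation or power is stated for the association objective.

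**Size of the grid.**
- Imagery scores: 4 (MIQ-3) + 2 (Orientate) + 2 (chronometry, each hand) = 8.
- Functional outcomes: Box and Block 1 + Jebsen-Taylor 7 + Functional Reach 1 + questionnaire 1 = 10. The 7 comes from the JTHFT Description: "Participants will be required to complete 7 distinct tasks".
- Joint-angle outcomes: 3 elbow + 2 shoulder = 5.
- Pairs: 8 × (10 + 5) = 120 with all imagery scores; 4 × 15 = 60 with the four MIQ-3 scores; 1 × 15 = 15 with the MIQ-3 total.

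Scoring the Jebsen-Taylor tasks for each hand would raise 120 to 8 × (17 + 5) = 176. Joint-position sides, modes and error types would raise it further. The check below does not use these.

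**Sample.** Textbox 2 does not say who enters the correlations. Residual limb length is measured only in amputees (Demographic Information) and missing data are deleted listwise, so the regressions as written retain at most 15 people. The correlations could use 15 or 30. Both are shown.

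**Critical correlation.** With k tests, α = 0.05/k and |r| must exceed t/√(t² + n − 2), where t is the two-sided critical value on n − 2 degrees of freedom. For k = 120, α = 0.05/120 = 0.000417:
- n = 15: t = 4.698, so |r| = 4.698/√(22.07 + 13) = 0.793.
- n = 30: t = 4.003, so |r| = 4.003/√(16.03 + 28) = 0.603.

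**Power for a true correlation of 0.6** (simulated Pearson correlations, bivariate normal data):

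| Tests in family | Critical r, n = 15 | Power, n = 15 | Critical r, n = 30 | Power, n = 30 |
|---|---|---|---|---|
| 120 | 0.793 | 10% | 0.603 | 51% |
| 60 | 0.768 | 15% | 0.577 | 60% |
| 15 | 0.705 | 28% | 0.518 | 75% |
| 2 | 0.575 | 59% | 0.409 | 92% |
| 1 | 0.514 | 70% | 0.361 | 96% |

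For a true correlation of 0.7 and 120 tests, power is 25% with n = 15 and 83% with n = 30. The true correlation needed for 80% power with 120 tests is about 0.86 (n = 15) or 0.69 (n = 30). For a single test it is about 0.66 or 0.49.

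**Dependence on the count.** With n = 15, an observed correlation between 0.705 and 0.768 is significant if 15 tests are counted and not significant if 60 or 120 are.

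**The case against.** The strongest reply is that 120 is one reading and not a floor. Textbox 2 speaks of correlations with MI and does not say that every imagery score meets every outcome. With the MIQ-3 as primary outcome, 60 or 15 pairs are defensible counts. Nor are the correlations expressly confined to amputees: a separate amputee-specific block has its own association analyses, which suggests that the two general blocks may cover both groups. Both points stand, which is why the size is given as a range.

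The Abstract's Conclusions and the end of Expected Outcomes do describe these relations as something to explore. That also stands. But Textbox 2 does not carry the label over: it attaches a correction, a .05 threshold and talk of prediction to these analyses.

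An unadjusted correlation followed by an adjusted regression is ordinary practice, and the exact Bonferroni family could be left to a fuller plan. What remains is that the article's own detailed analysis plan fixes Bonferroni over a broad grid, with two statements of its scope that differ and no pair given priority.

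A reader might also infer that the false-positive rate is uncontrolled. The documents do not support that: Bonferroni is stated twice, so testing everything at an uncorrected .05 is hypothetical, and so is a divisor built from the secondary outcome list. A reader might likewise infer that the SMMSE, BDI and VAS use up part of the correction. Textbox 2 plans no outcome test on any of them, so their listing is a labelling conflict only.

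**Conclusion.** The concern holds as one of poor power and an unfixed family. If Bonferroni covers all 120 pairs, power for a true correlation of 0.6 is about 10% with 15 amputees and 51% with all 30 participants. Two key pairs would give about 59% and 92%. On narrower readings of the grid the loss is smaller, but with 15 amputees and only 15 pairs power is still 28%.

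It would go too far to call the objective untestable. Correlations of about 0.86 with 15 people, or 0.69 with 30, would be detected with 80% power even at 120 tests. Nor does restructuring cure the sample size: with 15 amputees even a single prespecified pair reaches 80% power only at about 0.66.

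These figures assume Pearson correlations, bivariate normality and complete data. The true correlation of 0.6 is illustrative, since the documents give none.

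**What to change.** In Textbox 2:
- Name one key pair for function and one for proprioception: for example, one specified MIQ-3 score with the Box and Block Test, and the same score with one joint-position error averaged over the angles.
- State whether the correlation or the adjusted regression decides, and in which participants.
- Test the two key pairs with Holm at a family-wise 0.05. Holm is never less powerful than Bonferroni at the same error rate.
- Label all other pairs exploratory, in line with the article's own description, and report estimates with 95% confidence intervals.
- Make the multiplicity sentences in Outcome Measures and Textbox 2 agree with this.

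Separately, reconcile Outcome Measures with the SMMSE, BDI and VAS descriptions by listing these three as eligibility descriptors and not as secondary outcomes.

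The cost is wording. The Results section reports that no statistical analysis has yet been conducted, so the key pairs can still be chosen without sight of the results. The downside is small: the remaining pairs carry no significance claims, which the stated correction over the full grid would seldom have allowed with 15 amputees.

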### QuickDASH Questionnaire Description

The QuickDASH questionnaire will be used as a self-reported instrument designed to assess activity limitations and participation restrictions of the upper extremity [38]. The Turkish validity and reliability of the questionnaire were established by Düger et al [39]. The QuickDASH questionnaire consists of 11 items and aims to evaluate the level of difficulty individuals experience during daily living activities. Responses will be rated using a 5-point Likert scale (1=no difficulty, 2=mild difficulty, 3=moderate difficulty, 4=severe difficulty, and 5=unable to perform). Questionnaire scores will be recorded for both groups included in the study.

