### JPS Description

To evaluate proprioceptive function relevant to prosthetic control, the JPS assessment will be used. JPS measures an individual’s ability to replicate a given joint angle and can be conducted using combinations of passive and active movements, under eyes-closed conditions [22].

Considering the amputation levels of the individuals who have undergone transradial amputation, all participants will undergo JPS assessment of the shoulder and elbow joints, performed bilaterally (dominant and nondominant sides where applicable) with standardized positioning while standing comfortably with feet shoulder-width apart and arms relaxed at the side before each trial. In the amputee group, assessments will be conducted with the prosthesis worn and the terminal device maintained in the closed position to ensure consistency across participants. For passive JPS, the investigator will move the limb to the target angle (eg, 30°) and then return it to the starting position, and the participant will estimate the joint angle without moving it. Participants’ vision will be occluded during assessment to prevent visual feedback, ensuring blinding to the target angle. For active JPS, the investigator first demonstrates the target angle with the participant’s eyes open. Subsequently, with eyes closed, participants actively replicate the joint angle without any physical guidance.

For the shoulder joint, angles of 90° abduction and 90° flexion will be used; and for the elbow joint, angles of 30°, 60°, and 90° flexion will be assessed. All joints will be positioned consistently at the same starting reference point for each trial to ensure measurement consistency across participants. Each angle will be measured 3 times, and the mean value will be recorded. Trials with outlier values exceeding 2 SDs from the mean or trials with measurement errors will be excluded.

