**Amputee-specific analyses**
Dominant-side amputation will be coded as a binary variable (yes or no).Differences in MI, functional outcomes, and proprioception outcomes between participants with amputation of the dominant limb and participants with amputation of the nondominant limb will be analyzed using appropriate parametric or nonparametric tests.Associations with MI outcomes will be examined using correlation and regression analyses.

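### As written, the imagery–function and imagery–proprioception correlations are neither limited to amputees nor adjusted for group, so group differences alone could produce an association

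*Protocol article*

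**What the plan says.** The article presents Textbox 2 (Statistical Analysis) as its detailed analysis plan. The first block defines two groups, amputees and controls. Later blocks deal with association:

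- **MI and upper limb function.** "Correlations between MI and functional tests" are planned for the Box and Block Test, the Jebsen-Taylor subtests, the Functional Reach Test and the DASH questionnaire. They "will be analyzed using Pearson or Spearman correlation, depending on normality". Then: "Regression analyses will examine the predictive effect of MI on function, adjusting for age, dominance, and residual limb length".
- **Next block, MI and proprioception.** For five joint positions the plan sets out "Correlations between MI and proprioception measures". Then: "Regression models will evaluate predictors of proprioceptive performance, with covariates age, dominance, and residual limb length".
- **Amputee-specific analyses.** This block compares dominant-side with nondominant-side amputation and ends: "Associations with MI outcomes will be examined using correlation and regression analyses".

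The first two blocks name no analysis population and no group term. The covariate list at the end of JPS Description does not include group either. The data would allow a pooled analysis. For QuickDASH, "Questionnaire scores will be recorded for both groups included in the study". For joint position sense, "all participants will undergo JPS assessment of the shoulder and elbow joints". Under Demographic Information, stump length is measured only in participants with amputation. Textbox 2 handles missing data by listwise deletion.

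**The concern.** Figures 2 and 3 show amputees doing the Box and Block and Jebsen-Taylor tests with the prosthetic hand; controls use intact hands. The two groups may therefore form separate clusters on these tests. The study is also sized to find a large group difference in imagery. When both variables shift with group, a correlation over all 30 participants picks up the line joining the two group means. It can be clearly non-zero when imagery and function are unrelated among amputees and unrelated among controls. Choosing Spearman over Pearson does not help.

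The Objective and the Conclusions of the Abstract concern imagery in prosthesis users and look ahead to imagery-based training for them. A pooled coefficient that mainly restates the group comparison does not answer that question and could be taken as support for such training.

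There is also a mismatch of populations. A reader would take each regression as the adjusted version of the correlation beside it. If limb length is missing for every control, the regression contains amputees only, while an unrestricted correlation contains everyone.

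**Working it through.** The article gives no sample-size or precision figure for the correlations, so there is no stated result to reproduce. Whether 15 per group suits the primary comparison is a separate matter and is not used here.

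**Inputs**
- 15 per group, two-sided alpha .05 (Participants; Significance).
- Imagery group difference d1 = 0.8, the sizing assumption (Participants).
- Function group difference d2: not in the document. Assumed 2 to 4 within-group SD, with smaller values shown for contrast.
- Within-group correlation set to zero, within-group SDs equal.

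**Pooled correlation.** For two equal groups,

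r = (d1·d2/4) / √[(1 + d1²/4)(1 + d2²/4)]

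With d1 = 0.8, 1 + d1²/4 = 1.16:
- d2 = 2: 0.40/√(1.16 × 2) = 0.263
- d2 = 3: 0.60/√(1.16 × 3.25) = 0.309
- d2 = 4: 0.80/√(1.16 × 5) = 0.332

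**Chance of a significant result.** By Fisher z with N = 30, this is Φ(atanh(r)·√27 − z), with z = 1.960 at .05. For Bonferroni the article does not state the family size. Ten functional scores are assumed (Box and Block, seven Jebsen-Taylor tasks, Functional Reach, QuickDASH), so alpha = .005 and z = 2.807.

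| d2 | atanh(r)·√27 | P<.05 | P<.005 |
|---|---|---|---|
| 2 | 1.40 | 29% | 8% |
| 3 | 1.66 | 38% | 13% |
| 4 | 1.79 | 43% | 16% |

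Simulation at .05 (40,000 runs) gave 30%, 41% and 47% for Pearson and 31%, 40% and 43% for Spearman, so the Fisher figures are not exaggerated.

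**Dependence on the assumptions** (simulation, Pearson, unadjusted .05)
- d1 = 0.8 with d2 = 0.8: r = 0.14, rate 12%.
- d1 = 0.8 with d2 = 1.5: r = 0.22, rate 23%.
- d1 = 0.4 with d2 from 0.8 to 4: 7% to 16%.
- d1 = 0 or d2 = 0: 5%.

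**Remedies.** With a group term (N = 30) or in amputees only (n = 15), the rate is about 5% at every d1 and d2 tried.

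**Regressions** (d1 = 0.8, d2 = 2 to 3, 6,000 runs)
- Age and dominance only: 28% to 38%.
- Residual limb length added and coded 0 in controls: 7% to 8%, because it partly stands in for group.
- Controls dropped by listwise deletion: 5%.
- Group term in place of limb length: 5%.

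So under listwise deletion the regressions are not biased in this way, but they describe at most 15 people.

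**The case against.** The strongest reply is that pooling is inferred. No line says that all participants enter the correlations, and a journal article may leave the analysis set to a fuller document. The Objective can be read as concerning prosthesis users only, and adjustment for limb length fits that reading. This stands in part: a reader might infer that the plan commits itself to a pooled analysis, and it does not. But the article calls Textbox 2 its detailed plan and sets one block apart as amputee-specific, which implies that the others are not. Limb length does not settle it, because the same covariate appears in the between-group imagery comparison.

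A second reply is that amputee-only associations are already planned in the last line of the amputee-specific block. That line names no function or proprioception variable and does not restrict the blocks before it.

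A third reply concerns size, and most of it stands. The 2 to 4 SD difference is an assumption. Joint position sense is tested at the shoulder and elbow, above the amputation, and the document gives no group difference for it, for QuickDASH or for Functional Reach. The Discussion cites studies in which prosthesis users did about as well as healthy people on hand mental rotation, so the artefact may be small for that measure. A reader might use the cited d of 1.41 to obtain much larger correlations, but the article attributes that effect to a healthy population and does not plan on it. A reader might also quote the 29–43% alone, but the plan applies Bonferroni, which lowers the error rate per test. It does not remove the bias in r.

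**Conclusion.** The point holds as a conditional one. As written, both sets of correlations are open to all 30 participants without a group term, and the layout of Textbox 2 favours that reading without stating it. If they are pooled, and if imagery and the outcome both differ by group, the coefficient is non-zero with no within-group association. At d1 = 0.8 and an assumed d2 of 2 to 4, r is about 0.26 to 0.33, with a significant result in about 29–43% of studies unadjusted, or about 8–16% per test if Bonferroni covers ten tests.

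This is plausible for the Box and Block and Jebsen-Taylor tests. For QuickDASH, Functional Reach and joint position sense the document supports no figure, so it would be wrong to infer that the proprioception correlations are distorted to the same degree. The artefact disappears if either group difference is zero.

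The mismatch of populations is likewise conditional: under listwise deletion the regressions cover at most the 15 amputees, which differs from a pooled correlation but not from an amputee-only one.

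**What to change.** State in Textbox 2 that the association objective is answered in the amputee group, for correlations and regressions alike. Control-group coefficients can be reported separately. If a pooled estimate is also wanted, fit group and an MI-by-group term, omit residual limb length from that model, and report the slope within each group. Label any unadjusted pooled correlation as descriptive.

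This changes wording only. The Results section says that statistical analyses had not yet been run, so it can still be prespecified. The price is precision. By Fisher z, 80% power at two-sided .05 needs |r| of about 0.67 with 15 amputees, against about 0.50 with 30 participants. The smallest |r| that reaches P<.05 rises from 0.36 to 0.51. The amputee-only results should therefore be reported with confidence intervals and read as exploratory.
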